## Abstract

Previous work has demonstrated the protective effect of shoe cushioning on injury risk in leisure-time runners, but most models currently available on the market have greater cushioning than those investigated so far. Also, the optimal level of cushioning and the role of cushioning on the forepart of the shoe for injury prevention are still unknown. The main aim of this study is to determine whether (1) current ‘extra soft’ cushioning material at the rear part of the shoe reduces injury risk compared with stiffer material and (2) cushioning under the forepart of the shoe also contributes to injury risk reduction. This randomised trial with a 6-month intervention will involve 1000+ healthy leisure-time runners who will randomly receive one of the three running shoe versions. Study shoe versions will differ in their cushioning properties (ie, stiffness) at the rear or the forepart. Participants will self-report any lower limb or lower back problems on a dedicated electronic system every week, while the system will collect training data from the participant’s sports watch. Time-to-event analyses will be used to compare injury risk between the three study groups and to investigate the association between the runner’s characteristics, cushioning level and position, training and injury risk. The study was approved by the National Ethics Committee for Research (Ref: 202405/02 v2.0), and the protocol has been registered on https://clinicaltrials.gov/ (NCT06384872, 02/08/2024). Outcomes will be disseminated through presentations at international conferences and publications in peer-reviewed journals, popular magazines and specialised websites.

WHAT IS ALREADY KNOWN ON THIS TOPICWHAT THIS STUDY ADDSThis is the first randomised trial to investigate the effect of ‘extra soft’ cushioned shoes (about 40 N/mm) and cushioning location (ie, rear and forepart of the shoes, respectively) on running-related injury risk.HOW THIS STUDY MIGHT AFFECT RESEARCH, PRACTICE OR POLICYThe study outcomes will help better understand the relationship between the runner’s characteristics, cushioning level and location, training and injury risk.The study outcomes will also help the industry make important decisions for designing future running shoe models.

## Introduction

 Regular physical activity prevents chronic diseases and reduces all-cause mortality.^1^ In particular, vigorous-intensity aerobic physical activity has been shown to provide greater benefits for the risk of premature mortality.^2^ However, physical activity has declined globally for decades, largely driven by occupational, domestic and commuting physical activity reductions.^3^ The negative impact of an inactive lifestyle on health is one of the main motivations for adults to perform more physical activity during their leisure time.^4^ Long-distance running is one of the most popular physical activities across the world.^5^ Given the popularity of leisure-time running, its long-term mortality benefits,^6^ as well as the superior benefits running may confer over other types of vigorous-intensity physical activity for the prevention of chronic diseases and premature mortality,^7^ long-distance running appears to be one of the most cost-effective lifestyle interventions from a public health perspective.^8^

One of the main drawbacks of running is the high risk of sustaining a running-related injury,^9^ which is considered a major barrier to continued participation.^10^ Running-related injury incidence has remained high during the last 40 years, with an overall incidence rate of 50% per year.^11^ Most running-related injuries develop progressively, resulting from an imbalance between repetitive loading of the musculoskeletal system and tissue load capacity.^12^ More specifically, tissue microdamage resulting from repetitive loading is a stimulus for remodelling and adaptation. Yet, it may eventually lead to tissue failure (ie, tear, rupture, fracture) without appropriate repair.^13^

In relation to the repetitive loading of the musculoskeletal system, Body Mass Index has been associated with injury risk in runners.^14 15^ This observation suggests that the increased physical stress due to extra body weight affects injury risk. Surprisingly, body mass as such has hardly ever been considered as a potential risk factor for running injury.^9^ Despite the lack of evidence on the association between body mass and injury risk, it is a common belief that heavier runners should use footwear with increased shock absorption properties. Indeed, footwear cushioning as a modifiable factor has been shown to influence impact forces and loading rate during running.^16^ Nevertheless, only lighter runners benefited from greater cushioning in our previous study,^17^ which still confirms that the runner’s weight moderates the effect of shoe cushioning on injury risk.

Since repetitive loading of the musculoskeletal system has been viewed as a concern for injury risk during running, cushioning has been the most extensively investigated shoe feature. Different solutions of shoe cushioning have been developed to attenuate impact peak forces and loading rate, as these biomechanical characteristics are associated with the development of specific running injuries.^18^ The shock absorption properties of footwear mainly result from the materials used in the sole (ie, their type, density, structure and combinations thereof), as well as from the geometry of the shoe (ie, the midsole thickness and the design of inserts). Only a few prospective studies have investigated the impact of shoe cushioning on injury risk in running.^15 17 19^ One investigation compared different types of shoe insoles and found no difference in injury risk; however, the study involved Royal Air Force recruits, and the findings may not be generalised to runners.^19^ Another study with negative results compared two versions of a standard running shoe with a narrow difference in midsole hardness (15%) and limited sample size (n<250).^15^ The study limitations suggest that these findings should be interpreted cautiously, though. Our latest study on 800+ leisure-time runners provided evidence, for the first time, on the effectiveness of greater shoe cushioning (65 N/mm vs 95 N/mm) in reducing injury risk,^17^ as well as a plausible explanation for this protective effect.^20^ Nevertheless, the optimal amount of cushioning for injury prevention according to the runner’s individual characteristics remains unknown. Besides, the market has quickly evolved since the introduction of advanced footwear technology, especially regarding foam materials, which are ‘extra soft’ nowadays. The whole footwear range (from performance to cushioning and stability shoes) uses soft or extra soft foams. At the same time, it is unknown if this evolution of shoe technology impacts injury risk. Furthermore, the role of cushioning under the forepart of the shoe for injury prevention has never been investigated.

The comfort filter paradigm has previously been suggested as a new approach to reduce injury risk.^11^ Accordingly, the authors stated that a runner should select a comfortable product using his/her comfort filter. If this paradigm is valid, a relationship should exist between cushioning, comfort and injury risk, given the protective effect of greater cushioning previously reported.^17^ Furthermore, shoe cushioning has been reported to deteriorate with mileage,^21^ which may influence running biomechanics.^22^ Therefore, cushioning perception and comfort changes could inform on shoe deterioration and injury risk.

There is also a growing interest in the cumulated workload outside of scheduled training.^23 24^ Indeed, a 24-hour integrative perspective on training is potentially relevant for injury risk management, as conditions outside training significantly modulate the total workload and training adaptation and recovery. This could be even more relevant in leisure-time athletes due to a generally lower training volume and, thus, a relatively higher contribution of additional activities outside running training to tissue load. The quantification of the 24 hours weight-bearing and locomotion activities in runners may provide insight into the role of off-training behaviour on injury risk and highlight the need to control off-training activities in sports injury research. To our knowledge, no previous study has addressed this question.

## Objectives

The main purpose of this study is to investigate the effect of different cushioning solutions on injury risk in leisure-time running. The project focuses on the influence of cushioning properties at the rear and the forepart of the running shoes on musculoskeletal problems in leisure-time runners. The primary objective of this study is to determine whether ‘extra soft’ cushioning material (ie, global stiffness: 40±5 N/mm) at the rear part of the shoe reduces injury risk compared with stiffer material (ie, global stiffness: 60±5 N/mm) in leisure-time runners. The secondary objectives of this study are to investigate whether (1) cushioning under the forepart of the shoe also influences injury risk, independently of the cushioning at the rear part, (2) the effects of cushioning properties and position on injury risk depend on the runner’s body mass and (3) perception of cushioning is related to both shoe cushioning and injury risk. The present study will also explore (1) if other weight-bearing locomotion activities (ie, number of steps per day in addition to the steps from running) represent an independent risk factor for running-related injury, (2) the role of (biological) sex in injury mechanism, as previous work showed that injury risk and risk factors may be different in men and women,^25^ and its potential moderation effect, (3) how acute changes in training load affect injury risk and (4) if disparities in injury risk exist according to the socioeconomical status of the runners (eg, level of education, socioprofessional category, gross annual household income).

Our main hypothesis is that greater shock absorption properties at the rear part of standard running shoes are associated with lower injury risk in recreational runners. Our secondary hypotheses are (1) greater shock absorption properties under the forepart of the shoe are also associated with lower injury risk in recreational runners, (2) runners with low body mass experience a lower injury risk in shoes with greater shock absorption properties,^17^ and (3) greater perceived cushioning is related to lower injury risk.

## Methods

### Study design

This study is a randomised trial with an intervention period of 6 months to compare three running shoe versions, which differ with respect to their cushioning properties and position (ie, rear and forepart of the shoe). A renowned sports equipment manufacturer provides the running shoe versions. The participants, as well as the assessors, will be blinded to group allocation. The design of the trial is illustrated in figure 1. The protocol conforms to the Recommendations for Interventional Trials (SPIRIT, (online supplemental material 1), has been registered on https://clinicaltrials.gov/ (NCT06384872, 02/08/2024) and was approved by the National Ethics Committee for Research (CNER; Ref: 202405/02 v2.0)). Written informed consent will be obtained from all participants (online supplemental material 2).

**Figure 1 F1:**
[figure not shown]
Trial design.

### Study population

Healthy leisure-time runners will be recruited through advertisements in local newspapers and press releases within Luxembourg and via social media from January 2025 to June 2025. Participants will be informed that they will randomly receive one of the three study shoe versions to be worn during the intervention period for all their running activities. Healthy volunteers will be considered eligible if they are aged between 18 and 65 years, willing to use the study shoes for each running session (and only for running activities), use a sports watch for training data recording, are Strava users (or are willing to create an account) and signed the electronic informed consent. Volunteers will be excluded in case of any contraindication to running training, including cardiovascular/respiratory, any disease or running impeding injury/condition at the time of initial inclusion, a history of surgery to the lower limbs or, the lower back within the previous 12 months, any known degenerative conditions, the use of orthopaedic insoles for physical activity, or any running injury (ie, a physical pain or complaint related to running practice that causes the runner to interrupt or modify his/her training for at least 1 week) over the month before study inclusion. No limitation will be set regarding running experience, running level (performance), body mass or Body Mass Index.

### Intervention

The study shoes are prototypes derived from a model available on the market (Kiprun KS 500 2) and will be anonymised for the purpose of this trial. The soles of the shoes will be customised for the study. The three running shoe versions will have the same design, except for their cushioning properties at the rear and forepart of the shoe, which will differ by about 40% and 30%, respectively (figure 2). Nevertheless, cushioning properties will remain within the range of values of the shoes available on the market (linear equivalent stiffness: 40±5 to 60±5 and 60±5 to 80±5 N/mm, at the rear and forepart of the shoe, respectively). We expect a difference in shoe weight lower than 30 g between the three versions (for size 43). The difference in cushioning properties between shoe versions will be created by modifying the type of foam and the foaming process. A set of shoes (5 pairs per version, shoe size 43) will be tested for stiffness properties by the manufacturer according to a standardised protocol (Impact test: ASTM F1614, Procedure A)^26^ to provide accurate data on the technical specifications (stiffness and dissipated energy). The cushioning properties (linear equivalent stiffness) of the study shoe versions will be characterised as follows (see also figure 2): hard shoe version (‘Hard-Hard’—about 60±5 and 80±5 N/mm at the rear and forepart of the shoe, respectively), mixed shoe version (‘Soft-Hard’—about 40±5 and 80±5 N/mm) and soft shoe version (‘Soft-Soft’—about 40±5 and 60±5 N/mm). The main hypothesis will be tested by comparing the mixed shoe version with the hard shoe version, while the secondary hypothesis will be tested by comparing the soft shoe version with both the hard and mixed shoe versions.

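### The rear and forepart objectives are worded more broadly than the three shoe versions can test, and soft versus hard should not serve as a test of the forepart

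*Protocol article*

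**What the plan says.** The Intervention section of the protocol article defines three versions by rear and forepart stiffness: Hard-Hard, "about 60±5 and 80±5 N/mm at the rear and forepart of the shoe, respectively"; Soft-Hard (mixed), "about 40±5 and 80±5 N/mm"; and Soft-Soft, "about 40±5 and 60±5 N/mm". No version combines a hard rear with a soft forepart.

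The same section assigns the contrasts. For the rear: "The main hypothesis will be tested by comparing the mixed shoe version with the hard shoe version". For the forepart: "the secondary hypothesis will be tested by comparing the soft shoe version with both the hard and mixed shoe versions".

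The Objectives section is broader. The primary objective asks whether extra soft material "at the rear part of the shoe reduces injury risk compared with stiffer material", with no forepart stiffness named. The main hypothesis is that "greater shock absorption properties at the rear part of standard running shoes are associated with lower injury risk in recreational runners". The first secondary objective is whether "cushioning under the forepart of the shoe also influences injury risk, independently of the cushioning at the rear part". The Limitations section mentions neither the absent combination nor a possible rear-by-forepart interaction.

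**The concern.** Two gaps lie between the stated questions and the contrasts.

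First, each single-zone effect is observed at only one level of the other zone. A statement about the rear at any forepart stiffness, or about the forepart whatever the rear stiffness, needs the assumption that the two zones do not interact. The article does not state that assumption, and three versions cannot test it.

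Second, soft versus hard is named as a test of the forepart hypothesis, yet these shoes differ at the rear as well. A significant result there could come entirely from the rear, which is what the primary hypothesis already expects to matter. The trial could then report support for forepart cushioning with no forepart effect present. The abstract says the results will help industry design future shoes, so it matters which zone gets the credit.

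**Working it through.** **Inputs.** Stiffness values and contrasts come from Intervention. From Sample size: alpha 0.05, power 80%, average injury rate 30%, HR 1.50, drop-out 10%, 356 per group, 1068 in total. Sidedness is not stated. Two-sided is assumed because it reproduces the plan's figure; one-sided would give 839.

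**Reproducing the plan's figure.** Schoenfeld's formula for one pairwise comparison with equal arms:

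- Events = (1.960 + 0.842)² / (0.25 × (ln 1.5)²) = 191.
- Two arms: 191 / 0.30 = 637 evaluable participants.
- Three arms: 637 × 1.5 = 956 after rounding up; 956 / 0.9 = 1063 after rounding up.

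The stated 1068 is within 1% of this. The sample size therefore fits a single pairwise contrast and is not in question.

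**What each contrast changes (N/mm).**

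| Contrast | Rear | Forepart | What it estimates |
|---|---|---|---|
| Mixed vs hard | 60 to 40 | 80, fixed | Rear effect at forepart 80 |
| Soft vs mixed | 40, fixed | 80 to 60 | Forepart effect at rear 40 |
| Soft vs hard | 60 to 40 | 80 to 60 | Both together |

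Write R80 for the log hazard ratio of mixed versus hard and F40 for that of soft versus mixed. Then soft versus hard = R80 + F40. The rear effect at a 60 N/mm forepart, the forepart effect at a 60 N/mm rear, and the interaction cannot be estimated at any sample size.

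**Soft versus hard as a forepart test.** Suppose there is a pure rear effect at the planned size and no forepart effect, with the hazard ratio for softer against stiffer taken as 1/1.5:

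- R80 = ln(1/1.5) = −0.405 and F40 = 0, so soft versus hard = −0.405, a hazard ratio of 0.67.
- Events in two arms = 356 × 2 × 0.9 × 0.30 = 192.2.
- Power = Φ(√(192.2 × 0.25) × 0.405 − 1.960) = Φ(2.811 − 1.960) = Φ(0.851) = 80%.
- Soft versus mixed has a true hazard ratio of 1, so it favours the softer shoe significantly in 0.05 / 2 = 2.5% of trials.

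With no forepart effect at all, one of the two listed forepart tests would be positive about 80% of the time and the other 2.5%.

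**Scope of the rear claim (assumed values, for illustration).** Take a rear hazard ratio of 0.67 at an 80 N/mm forepart. If the ratio of rear hazard ratios (forepart 60 against forepart 80) were 0.75, the rear hazard ratio at a 60 N/mm forepart would be 0.67 × 0.75 = 0.50. If that ratio were 1.33, it would be 0.67 × 1.33 = 0.89. The trial's data would look the same in both cases.

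**The case against.** The strongest reply is that the design is sound and openly described. Each of the two single-zone contrasts changes one zone and holds the other fixed, and participants are randomised, so each is a valid causal estimate. The forepart objective's claim of independence can be read simply as holding the rear constant, and soft versus mixed answers that. A three-step sequence of shoes is a legitimate choice, and no section expresses interest in a 60/60 shoe. All of this stands. It is why the point concerns wording and the assignment of one contrast, not a missing arm.

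A reader might infer more, in three ways that the documents do not support:

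- *That neither the rear nor the forepart claim can be supported.* Both conditional effects are estimable, and both general claims follow if the zones do not interact.
- *That the mixed shoe's larger difference between forepart and rear stiffness confounds the primary contrast.* The nominal differences are 20, 40 and 20 N/mm, but each is just forepart minus rear, so softening the rear at a fixed forepart must change it. Nothing in the article gives it a separate effect on injury.
- *That a null primary result should be read beside soft versus hard.* That would lend weight to a contrast in which both zones change and invite rescue of a failed primary.

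One reservation concerns the 80% figure. The article does not say whether the forepart hypothesis needs one or both of its contrasts to be positive. If both were required, soft versus mixed would limit false support to at most 2.5% in the favourable direction. The 80% applies if soft versus hard alone may count as support. Holding the rear constant also does not rescue soft versus hard, because there the rear is not constant.

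**Conclusion.** The point holds as a matter of scope and contrast assignment. The trial identifies the rear effect at an 80 N/mm forepart and the forepart effect at a 40 N/mm rear. Objectives words both without those conditions, and Intervention adds a forepart test that does not isolate the forepart. With a pure rear effect of HR 1.5, that added test would be significant about 80% of the time.

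The figure rests on the plan's own inputs (30% average injury rate across the two arms compared, 10% drop-out, 356 per group), a two-sided 5% test, and Schoenfeld's approximation for a pairwise Cox comparison. The planned analysis uses Fine-Gray models, so the exact power may differ somewhat. The finding casts no doubt on the primary contrast as a randomised comparison or on the sample size.

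**What to change.** In Objectives and Intervention:

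1. Define the primary objective and main hypothesis as the effect of a 40 versus 60 N/mm rear in shoes with an 80 N/mm forepart, tested by mixed versus hard.
2. Define the forepart objective and its hypothesis as the effect of a 60 versus 80 N/mm forepart in shoes with a 40 N/mm rear, tested by soft versus mixed only. Replace the word *independently* and its qualifier with *with rear stiffness held at 40 N/mm*.
3. Keep soft versus hard, but report it as the effect of softening the whole shoe and not as a test of the forepart.

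The cost is a few sentences and a narrower claim. No arm, participant, measurement or change of sample size is needed.

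### The forepart hypothesis is assigned two contrasts; one of them, Soft-Soft versus Hard-Hard, also changes the rear, and the protocol does not say which contrast carries the conclusion

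*Protocol article*

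**What the plan says.** The Objectives section of the protocol article sets as its first secondary question whether "cushioning under the forepart of the shoe also influences injury risk, independently of the cushioning at the rear part". The matching hypothesis is that "greater shock absorption properties under the forepart of the shoe are also associated with lower injury risk in recreational runners".

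The Intervention section gives the linear equivalent stiffness of the three shoes, rear first and forepart second:

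- Hard-Hard (hard version): "about 60±5 and 80±5 N/mm at the rear and forepart of the shoe, respectively"
- Soft-Hard (mixed version): "about 40±5 and 80±5 N/mm"
- Soft-Soft (soft version): "about 40±5 and 60±5 N/mm"

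The same section assigns contrasts to hypotheses. For the rear: "The main hypothesis will be tested by comparing the mixed shoe version with the hard shoe version". For the forepart: "the secondary hypothesis will be tested by comparing the soft shoe version with both the hard and mixed shoe versions". It gives no rule for combining or ranking the two secondary comparisons.

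**The concern.** The objective asks for the forepart effect with the rear taken out of the picture. One of the two contrasts named for it does not do that, because Soft-Soft and Hard-Hard differ at both ends of the shoe. A difference between them could come from the rear alone, the forepart alone, or both.

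This matters because a rear effect is the trial's own main hypothesis. The situation in which soft versus hard would mislead about the forepart is the one the trial is sized to detect. Without a stated rule, the same data could support or not support a forepart claim, depending on which comparison the report leans on.

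**Working it through.** **1. What each contrast changes (N/mm, nominal values from Intervention)**

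| Contrast | Rear | Forepart | Isolates |
|---|---|---|---|
| Mixed vs hard | 60 to 40 | 80, fixed | rear |
| Soft vs mixed | 40, fixed | 80 to 60 | forepart |
| Soft vs hard | 60 to 40 | 80 to 60 | neither |

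**2. Reproducing the sample size.** Inputs from Sample size: alpha 0.05 (taken as two-sided), power 80%, HR 1.50, injury rate 30%, drop-out 10%, equal arms. Schoenfeld's formula for a 1:1 pair:

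- Events = (1.960 + 0.842)² / (0.25 × (ln 1.5)²) = 190.97, so 191.
- Participants in two arms = 191 / 0.30 = 637. Allowing for drop-out, 637 / 0.90 = 708, or 354 per arm.
- Three arms = 3 × 354 = 1062, against 1068 stated (0.6% apart). The plan's figure is reproduced as a pairwise calculation.

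**3. Events per pair at the stated size.** 2 × 356 × 0.90 × 0.30 = 192.2.

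**4. Scenario: the rear matters and the forepart does not.** Hard-Hard versus Soft-Hard has HR 1.50 (the planning value) and Soft-Hard versus Soft-Soft has HR 1.00. Soft versus hard then has HR 1.50 as well.

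- P(soft vs hard significant) = Φ(√(192.2/4) × ln 1.5 − 1.96) = Φ(2.81 − 1.96) = 0.803.
- With an assumed rear HR of 1.25: Φ(√(192.2/4) × ln 1.25 − 1.96) = Φ(1.547 − 1.96) = 0.34.
- P(soft vs mixed significant) = 0.05, two-sided, because the null is true for that contrast.

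**5. Joint behaviour.** The two contrasts share the soft arm, so they were simulated together (200,000 draws of the three arm log-hazards under a normal approximation; expected events 112, 80 and 80 in hard, mixed and soft). At a rear HR of 1.50:

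| Rule for claiming a forepart effect | Chance of a false claim |
|---|---|
| Soft vs hard alone is enough | 0.79 (0.80 by formula) |
| Either contrast is enough | 0.79 to 0.81 |
| Soft vs mixed only | 0.05 two-sided |
| Both required | 0.03 |

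The range in the second row is one direction only (0.79) against two-sided (0.81). If only results favouring the softer forepart count, the last two rows are both about 0.026.

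**The case against.** The strongest reply is that the isolating contrast is already prespecified. The protocol does not rest the forepart question on soft versus hard alone, and the word both in the Intervention section can be read as requiring both comparisons to agree. On that reading the false-claim rate is about 3%. A reader might infer that the plan commits the trial to reporting a rear effect as a forepart effect. The text does not support that, because it has no rule by which soft versus hard suffices or overrides a null soft-versus-mixed result. This part of the reply stands. What remains is that no rule is stated, and one of the two named tests does not match its objective. Requiring both would limit the error only through the clean contrast; the other adds nothing specific to the forepart.

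Second, the section speaks of one secondary hypothesis while Objectives lists three. The other two concern body mass and perceived cushioning, so the forepart hypothesis is much the likeliest target, but this is an inference.

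Two further criticisms are tempting and do not amount to errors:

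- There is no shoe with a hard rear and soft forepart, so the forepart effect can be estimated only with a soft rear. But holding the rear constant is an ordinary meaning of independence from it, and the protocol claims no interaction estimate.
- The Abstract puts under the main aim the question whether "cushioning under the forepart of the shoe also contributes to injury risk reduction". Objectives, Intervention and Sample size nevertheless give a consistent order, with the rear primary and the forepart secondary.

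**Conclusion.** The concern holds as a mismatch between a stated objective and one of its two stated tests, with the deciding contrast left open. If only the rear matters, the chance of a false forepart claim runs from about 3% to about 80%, depending on a rule the protocol does not give. The upper figure needs two things: soft versus hard (alone or as one of two sufficient contrasts) must count as forepart evidence, and the rear effect must be as large as the planning HR of 1.50. For soft versus hard alone it falls to about 34% at an assumed HR of 1.25.

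The figures also assume a 30% injury rate, 10% drop-out, a two-sided alpha of 0.05, and the Cox-type approximation behind the sample size rather than the planned Fine-Gray model.

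The primary comparison, mixed versus hard, changes only the rear and is unaffected. The point should be fixed, but it concerns one secondary hypothesis.

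**What to change.** In the Intervention section, name soft versus mixed as the sole test of the forepart hypothesis. Keep soft versus hard, but report it as the combined effect of softening rear and forepart, and say that it is not evidence on the forepart. Optionally, state in Objectives that the forepart effect is estimated with a soft rear (40±5 N/mm).

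The cost is a change of wording in the protocol and analysis plan. Arms, data collection and sample size stay as they are. The rule should be settled before any group comparison is run.
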